## Abstract

**Background:**

Life-skills trainings conducted within the school curriculum are effective in preventing the onset and escalation of substance use among adolescents. However, their dissemination is impeded due to their large resource requirements. Life-skills training provided via mobile phones might represent a more economic and scalable approach. The main objective of the planned study is to test the efficacy of a mobile phone-based life-skills training to prevent substance use among adolescents within a controlled trial.

**Methods/design:**

The efficacy of a mobile phone-based life-skills training to prevent substance use among adolescents will be tested in comparison to an assessment only control group, within a cluster-randomised controlled trial with two follow-up assessments after 6 and 18 months. The fully automated program is based on social cognitive theory and addresses self-management skills, social skills, and substance use resistance skills. Participants of the intervention group will receive up to 4 weekly text messages over 6 months in order to stimulate (1) positive outcome expectations, e.g., on using self-management skills to cope with stress, (2) self-efficacy, e.g., to resist social pressure, (3) observational learning, e.g. of interpersonal competences, (4) facilitation, e.g., of strategies to cope with negative emotions, and (5) self-regulation, e.g., by self-monitoring of stress and emotions. Active program engagement will be stimulated by interactive features such as quiz questions, message- and picture-contests, and integration of a friendly competition with prizes in which program users collect credits with each interaction. Study participants will be 1312 students between the ages of 14 and 16 years from approximately 100 secondary school classes. Primary outcome criteria will be problem drinking according to the short form of the Alcohol Use Disorders Identification Test and cigarette smoking within the last 30 days preceding the follow-up assessment at month 18.

**Discussion:**

This is the first study testing the efficacy of a mobile phone-based life-skills training for substance use prevention among adolescents within a controlled trial. Given that this intervention approach proves to be effective, it could be easily implemented in various settings and would reach large numbers of young people in a cost-effective way.

**Trial registration:**

ISRCTN41347061 (registration date: 21/07/2018).

## Background

Several biological, psychological, and social transitions that occur during adolescence are essential for a young person’s later-life trajectory [1, 2]. These transitions offer opportunities for them to gain skills to achieve greater autonomy from adults, build social connections with peers, develop a positive body image, and form a sense of identity. However, these transitions also facilitate exploration and risk taking at a stage when cognitive functions of the brain are not yet fully developed [3]. Shifts of emotional regulations and increased risky behaviours result in vulnerabilities for mental and substance use disorders, which constitute the biggest contributors to the health burden of 10- to 24-year-old individuals [4]. Substance use and the development of substance use disorders often first emerge during adolescence and co-occur with mental disorders [1]. The Swiss data of the Health Behaviour in School-aged Children (HBSC) study [5] showed noticeably increases in the lifetime prevalence of alcohol, tobacco and cannabis consumption over the age groups of 11-to-15-year-olds. The prevalence of regular cigarette smoking (weekly or daily) increased from 2% among 13-year old boys to 12% among 15-year-old boys and from 2% in 13-year old girls to 9% in 15-year old girls. The prevalence of binge drinking increased from 19% in 14-year old boys to 27% in 15-year old boys and from 14% in 14-year old girls to 23% in 15-year old girls.

A systematic review of studies assessing the effectiveness of prevention, early intervention, and harm reduction in young people for tobacco, alcohol, and illicit drugs demonstrated the effectiveness of taxation, public consumption bans, advertising restrictions, and minimum legal age, as well as the potential effectiveness of preventative interventions that deliver life-skills training in educational settings [6]. Schools are particularly suitable settings to reach adolescents with preventative interventions because of the ease of delivery and access to young people within compulsory secondary education. A Cochrane Review on school-based programs for the prevention of tobacco smoking [7] concluded that combined social competence and social influence interventions had a significant effect at 1 year and at longest follow-up (OR 0.49, 95% CI 0.28 to 0.87), whereas a social influences program on its own, multimodal community-wide initiatives, and information-only interventions were found to be ineffective. Another Cochrane review on school-based prevention programs for alcohol misuse in young people [8] concluded that certain generic psychosocial and developmental prevention programs can be effective. However, the methodological quality of the trials included in the analysis was poor, and this did not allow for any quantitative pooling of data.

The majority of the generic programmes addressing social competences and social influences which were included in the above-cited reviews can be described as life-skills trainings and primarily rely on Bandura’s social learning theory [9] which hypothesizes that children and adolescents learn substance use by modelling, imitation, and reinforcement, influenced by individual cognitions, attitudes. Furthermore, based on the social influences approach, [10] substance use susceptibility is increased by poor personal and social skills and young people initiate drug use as a result of pressure from peers, family and the media.

Generic life skills programs to prevent substance use, like the IPSY program, developed in Germany [11] or the ALERT [12] or Life Skills Training [13] programs developed in the US, typically combine training in self-management skills (e.g., coping with stress, emotional self-regulation, goal setting), social skills (e.g., assertiveness, communication skills) and substance use resistance skills (e.g. resisting peer pressure to drink alcohol, recognizing and resisting media influences promoting cigarette smoking, normative expectations about substance use).

Although these life-skills training programs were effective at preventing the onset of specific substances [7, 11, 14] or at decreasing problematic substance use [8], their implementation and dissemination in schools present serious challenges [15]. First, teachers and other professionals need the time, motivation, knowledge and skills to deliver the program. Second, extensive resources, in terms of personnel, money, and time allocated to deliver substance use prevention, are required to prepare and administer such programs.

Electronically-delivered interventions (e.g. via computer, Internet or mobile phone) have the potential to overcome the above-mentioned obstacles that hinder successful program implementation and larger-scale dissemination of life-skills training in schools. Electronically-delivered interventions have a wide reach at a low cost, and offer the opportunity to automatically deliver individually-tailored contents that can be accessed at any time and in any place [16]. Furthermore, electronically-delivered interventions might be more appealing for adolescents, because they can better ensure privacy and tailor contents to their needs.

A recent systematic review of alcohol and other drug prevention programs facilitated by computers or the Internet [17] identified nine trials of online prevention programs, of which six demonstrated significant, but modest effects for alcohol and/or other drug use outcomes. The programs were delivered in the US, Australia and the Netherlands and provided between 1 and 12 online curriculum-based standard lessons or tailored feedback. All programs were universal, i.e., delivered interventions to all students regardless of their level of risk, and were primarily based on principles of the social learning theory [9], the social influences approach [10] and the social cognitive theory [18, 19].

Beyond traditional personal computers, a promising means of delivering prevention programs is to do so remotely through the use of mobile technologies. In Switzerland, as in most other developed countries, almost all (98%) adolescents between the ages of 12 and 19 own a mobile phone, and 97% of these phones are smartphones [20]. Most adolescents are familiar with how to use mobile phones and typically use them on a daily basis for texting, taking pictures, playing games etc. Mobile phone-based interventions can provide almost constant support to users, in comparison to interventions that can only be accessed at specific times or locations and they provide a discrete and confidential means of intervention delivery [21]. Particularly mobile phone text messaging is a suitable means of delivering individually tailored messages via mobile phone. This interactive service allows cost-effective, instantaneous, direct delivery of messages to individuals. Several recent reviews underline the potential and efficacy of text messaging-based interventions in various health domains (e.g., diabetes self-management, weight loss, physical activity, smoking cessation, and medication adherence) and for different target groups, including adolescents and young adults [22–25].

Within a pre-post study in Switzerland, the acceptance and potential effectiveness of a mobile phone-based life-skills training program for substance use prevention among non-smoking vocational school students was tested [26]. This program was based on social cognitive theory and addressed self-management skills, social skills, and substance use resistance skills. Program participants received up to 3 weekly text messages over 6 months. Active program engagement was stimulated by interactive features such as quiz questions, message and picture-contests, and integration of a friendly competition with prizes in which program users collected credits with each interaction. A total of 1067 vocational students who owned a mobile phone and were not regular cigarette smokers were invited to participate in the program. Of these, 877 (82.2%) participated in the program and the associated study. Pre-post comparisons revealed decreased perceived stress and increases in several life skills addressed between baseline and the follow-up assessment. The proportion of adolescents with at-risk alcohol use significantly declined from 20.2% at baseline to 15.5% at follow-up.

Based on these results, showing high-level acceptance and promising effectiveness of a mobile phone-delivered life-skills training program among vocational school students, a reasonable next step is to test the efficacy of this interventional approach within a controlled trial. However, as the age of onset of substance use is strongly increasing between the ages of 14 and 16 [5], it might be even more appropriate to test this universal prevention approach among secondary school students.

Within this study protocol, we describe a cluster randomised controlled trial testing the efficacy of a similar mobile phone-based life-skills training program to prevent substance use among secondary school students.

## Methods/design

### Design and hypotheses

A two-arm cluster-randomised controlled trial will be conducted to test the efficacy of the *SmartCoach*, a mobile phone-based life-skills training program to prevent substance use among secondary school students. The efficacy of the intervention will be tested in comparison to an assessment only control group. The study participants will be assessed at baseline and at 6- and 18-months follow-up (Fig. 1). Our main hypothesis is that the individually tailored intervention program with a duration of 6 months will be more effective than assessment only, to prevent the onset and escalation of problematic alcohol and tobacco use at 18-months follow-up.

**Fig. 1 Fig1:**
[figure not shown]
Study design

### Participants, setting and procedure

We will test the intervention in secondary school students aged between 14 and 16 (grades 8 and 9). In this age group the prevalence of experimental and regular use of alcohol, tobacco and cannabis is increasing noticeably [5]. However, only a minority has established problematic or disordered substance use [5, 27]. Furthermore, nearly all adolescents at this age are familiar with how to use mobile phones and typically use them on a daily basis. According to the latest representative survey on media use in adolescents in Switzerland, 98% of the adolescents aged 14 and 15 years own a mobile phone and 98% use a mobile phone daily or several times per week [20]. Secondary schools in the German speaking part of Switzerland will be invited to participate in the study by cooperating regional centres for addiction prevention.

Employees of the above-mentioned centres for addiction prevention will arrange information sessions with a duration of 60 min in participating secondary school classes during regular school lessons reserved for health education. These information sessions will be led by junior scientist from the Swiss Research Institute for Public Health and Addiction, who are experienced in the work with young people, the provision of preventive interventions and trained on the study and on the program to be delivered.

The parents of the secondary school students in participating classes will be informed at least 1 week in advance of this session. They will receive a letter including information about the study and the intervention program and the parents are asked to give written informed consent to their child’s participation in the study.

Within the first half of the information sessions in the school classes, the junior scientist will raise awareness on the importance of life skills to effectively cope with the demands and challenges of everyday life. For this purpose, they will use video sequences demonstrating typical stressors and demands for this age group (e.g., search for an apprenticeship, exam stress, peer pressure for substance use) and different strategies to cope with them. The importance of emotional regulation skills and social competences to effectively cope with these stressors will be discussed based on case vignettes. Subsequently, the students will be informed about and invited to participate in a study testing innovative channels for the provision of life-skills trainings. To ensure sufficient participation and, thus, representativeness of the sample [28], a reward of 10 Swiss Francs for participation in each of the two follow-up assessments will be announced.

Students (1) with minimum age 14, (2) who own a mobile phone and (3) providing parental informed consent will be invited to participate in the study. Using their own or a provided mobile phone, informed consent will be obtained online from the study participants. Subsequently, they will be invited to choose a username, to provide their mobile phone number and to fill in the baseline assessment directly on the mobile phone.

Participants of the intervention group will receive additional questions which are necessary for the tailoring of the intervention content. Furthermore, for participants of the intervention group, the mobile phone-based intervention program and its association with a friendly competition will be described in detail. Subsequently, participants of the intervention group will receive an individually tailored web-feedback directly on their mobile phone (see also section intervention). During the subsequent 6 months, participants of the intervention group will receive the individually tailored mobile phone-based life-skills training.

Participants of the assessment only control group will be thanked for their study participation, they will be informed about their group assignment and their reward for participation in the follow-up assessment.

Follow-up assessments after 6 and 18 months will be conducted by a research assistant, within the participating school classes, during regular school lessons and using tablet computers. Computer-assisted telephone interviews will be conducted by a research assistant when assessments cannot take place during a school lesson because of vacations, class resolution, or study participants’ absence from class.

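### If classes dissolve after grade 9, a substantial share of the month-18 primary outcomes could come from oral telephone interviews instead of self-completion

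*Protocol article*

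**What the plan says.** The population is "secondary school students aged between 14 and 16 (grades 8 and 9"), according to Participants, setting and procedure. Neither the split between grades nor the time of year at baseline is given.

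Under Design and hypotheses, "The study participants will be assessed at baseline and at 6- and 18-months follow-up". The abstract places the primary outcomes at the later visit; the second of them is "cigarette smoking within the last 30 days preceding the follow-up assessment at month 18".

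At baseline, students are asked "to provide their mobile phone number and to fill in the baseline assessment directly on the mobile phone". Both follow-ups take place "within the participating school classes, during regular school lessons and using tablet computers". The alternative is an interview: "Computer-assisted telephone interviews will be conducted by a research assistant when assessments cannot take place during a school lesson". The listed reasons are holidays, a class that has been dissolved, and a student's absence. No self-administered alternative outside class is offered.

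Under Assessments and outcomes, the AUDIT-C, which defines the first primary outcome, is to be supported by pictures showing the size of a standard drink.

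**The concern.** Eighteen months is longer than a school year, and the sample comes from grades 8 and 9. The protocol also names the search for an apprenticeship as a typical stressor of these students, which suggests that many are near the end of compulsory school. In-class completion may therefore be unavailable to many of them at the visit that carries the primary outcomes.

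Those students would go straight to an interview, so an adolescent would report drinking and smoking aloud to an adult research assistant. Baseline and in-class follow-up use self-completion. A voice call also cannot show the standard-drink pictures, and the protocol names no substitute. For everyone phoned, the first primary outcome would not be measured as specified, whatever the share phoned.

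If oral reporting lowers disclosure, the observed event rates fall and power falls with them. If it lowers disclosure more in one arm, the contrast itself is affected.

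**Working it through.** **1. The plan's own figures.** Control smoking is 22% and the OR is 0.60. The intervention odds are 0.60 × 0.22/0.78 = 0.1692, so the intervention rate is 14.47%. At 80% power and two-sided 5%, the unpooled formula gives 410 per group, as stated. The design effect is 1 + 12 × 0.05 = 1.60; 410 × 1.60 = 656 per group and 1312 in total. The sample size reproduces and is not in question.

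**2. Who is past grade 9 at month 18.** Let t be the months into the school year at baseline, and L the month in which lessons end (assumed 10 to 11.5).

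- A grade-9 class is still in grade 9 only if t + 18 ≤ L, which is impossible.
- A grade-8 class is in grade 9 at month 18 only if t + 18 ≤ 12 + L, so t ≤ L − 6, that is 4 to 5.5 months.

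**3. Share out of class.** Assume that classes dissolve after grade 9. Let g be the grade-9 share of the sample and h the share of grade-8 students out of class. The overall share is g + (1 − g)h. Both g and the calendar are assumptions.

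| Baseline timing | h | g = 25% | g = 50% |
|---|---|---|---|
| Months 0-4 only | 0 | 25% | 50% |
| Even over months 0-10 | 0.45-0.60 | 59-70% | 72.5-80% |
| Months 5-10 only | 0.90-1.00 | 92.5-100% | 95-100% |

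The extremes are 0% (all grade 8, early baseline) and 100% (all grade 9).

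**4. Equal under-reporting by phone.** Let f be the share phoned and s the proportion of true smokers who report smoking by phone (assumed 0.7-0.9; the documents give no value). Observed prevalence = p[1 − f(1 − s)]. Power is the two-proportion normal approximation at the planned effective 410 per group.

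| f | s | Control | Intervention | Power | Observed OR |
|---|---|---|---|---|---|
| 0 | – | 22.0% | 14.5% | 80% | 0.600 |
| 0.25 | 0.9 | 21.5% | 14.1% | 79% | 0.602 |
| 0.25 | 0.7 | 20.4% | 13.4% | 76% | 0.605 |
| 0.50 | 0.9 | 20.9% | 13.8% | 77% | 0.603 |
| 0.50 | 0.7 | 18.7% | 12.3% | 72% | 0.610 |
| 0.75 | 0.9 | 20.4% | 13.4% | 76% | 0.605 |
| 0.75 | 0.7 | 17.1% | 11.2% | 67% | 0.615 |

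**5. Unequal under-reporting, for illustration.** Take no true effect, 22% in both arms, s = 0.85 in control and 0.75 in intervention.

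- f = 0.50: 20.35% against 19.25%, OR 0.93.
- f = 0.75: 19.53% against 17.88%, OR 0.90.

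This shows what a 10-point difference would do. It is not evidence that such a difference exists.

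**The case against.** **The situation was foreseen.** Class resolution is a listed reason for telephoning, and the text sets a rule for each mode without predicting a share. That stands: the issue is the choice of fallback, not an oversight.

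**A reader might infer that telephone will be the main mode.** The documents do not support this. They do not say when classes end, how the grades split or when baseline takes place. With early baseline only, telephone exceeds half only if grade 9 makes up more than half the sample. The sample size section expects students to be 16 at month 18, so about 16 − 1.5 = 14.5 at baseline. That is near the bottom of the enrolled range and may point to more grade-8 students.

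**A reader might infer that the treatment comparison is biased.** This is not shown either. The mode rule is common to both arms, randomisation is stratified by school, outcome assistants are blinded, and the analysis includes a group-by-time term with a concurrent control. Equal under-reporting at 50-75% phoned moves the OR only from 0.60 to 0.603-0.615. Participants know their arm and could shade their answers, or reveal their arm, in class too. Chance differences in mode between arms are ordinary imbalance.

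**The power figures rest on assumed sensitivities.** That is correct. The 67% is the extreme corner of the range.

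None of this answers the missing pictures. Nor does it explain why an oral interview should come before a self-administered form that already exists for phones.

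**Conclusion.** The point holds in conditional form. From the protocol's own grades and timing, month 18 falls after grade 9 for all grade-9 entrants and for later-enrolled grade-8 entrants. If classes dissolve then, a substantial share of the primary outcomes could move to oral report, and possibly most of them.

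The likely cost is inconsistent measurement and under-reporting. Under the assumed sensitivities, power for smoking would be 76-79% at a 25% phone share and 67-77% at 50-75%, against the planned 80%. Smoking is the tighter of the two primary outcomes, since problem drinking needed only 370 per group. The loss of the AUDIT-C pictures needs no assumed sensitivity and applies to every student phoned.

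Bias between arms arises only if reporting by phone differs by arm. This is possible because participants know their allocation and the intervention arm receives resistance messages and alcohol-use monitoring, but nothing in the documents establishes it. The change is worth making; confidence is medium because the grade split, calendar and class end are not stated.

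**What to change.** Amend the follow-up procedure in Participants, setting and procedure:

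- For students not reached in class, first send a personal text-message link to the same self-administered questionnaire, including the standard-drink pictures. The mobile number and a questionnaire for phones are already in place from baseline.
- Keep the telephone interview for those who do not complete the link.
- Record the mode of each assessment.

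Any comparison by mode should be descriptive or supportive only. Mode is settled after randomisation, so an analysis restricted to self-completed data would select on response.

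The cost is a wording change, one extra contact step and a short delay before non-responders are phoned. Completion through a link is unsupervised, unlike in class, but it keeps self-completion and the pictures. If few students turn out to need it, little is lost.
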